### 2.4. Intervention

Volunteers allocated to Group A and B will have access to a health management app. The app has functions of recording and monitoring the participants’ diet and exercise daily. The interventions include mobile-based nutrition interventions and exercise interventions. 

The nutrition interventions require the subjects be provided with 20 g of the professional meal replacement powders (Huaruizhongjian Biotechnological Co., Ltd., Shandong, China), 200 mL milk and 5 mL flaxseed oil for their breakfast and dietary guidance based on Mediterranean diet for their lunch and supper. The meal replacement powders include 10 g of meal replacement powders rich in minerals (4.50 g protein, 0.09 g fat, 1.26 g carbohydrate and 3.00 g dietary fiber with 125 kJ in total energy) and 10 g of meal replacement powders rich in vitamins (4.65 g protein, 0.11 g fat, 1.05 g carbohydrate and 3.18 g dietary fiber with 126 kJ in total energy). The dietary guidance will be through individual sessions with nutritionists using mobiles, including healthy food choices and portion sizes, 3 to 5 times per week depending on the participants’ compliance. The diets will be tracked and recorded through uploading the food logs and pictures of their three meals per day using the health management app under the supervision of the investigators in the background. 

The exercise interventions require the subjects be provided with exercise guidance and complete around 20 min of aerobic exercise, 20 min of resistance exercise and at least 6000 steps every day. The exercise guidance will be through individual sessions with exercise instructors, including exercise choices, duration and intensity, 3 to 5 times per week depending on the participants’ compliance. If the participants feel a little tired after the exercise and comfortable for the next day, the exercise intensity will be the best. The everyday steps of the subjects will be tracked and recorded through the sports bracelet and the aerobic exercise and resistance exercise logs and pictures will be uploaded using the mobile app, which will be supervised by the investigators in the background. 

Participants in Group A will receive nutrition interventions and exercise interventions for three months. Group B will receive exercise interventions for three months and Group C, the control group, will not be intervened and expected to follow their routine lifestyle as before. Interventions will be started one week after the enrollment.

The app and sports bracelet training will be provided in the same manner for both Group A and Group B volunteers one week before the start of this trial. The researchers will help the participants download the health management app through the smart phone app store and teach them to use the app and the sports bracelet. After the participants have learnt how to use the app and the bracelet, they will be asked to record their dietary data and physical exercise intensity following their old way of life for one week before the start of the intervention using the app and the bracelet, to guarantee that they have already grasped the usage of the app and the bracelet. As this is lifestyle intervention, the medication for the baseline chronic diseases will not be changed during the course of the study.

### 2.5. Follow-Up

All participants of this study will be followed-up for the duration of the intervention (three months). Participants may discontinue the trial at their request. If a participant does not meet the requirements of the study, he should also discontinue the trial. 

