### 2.6. Procedures

A summary of this trial is presented in Table 1. The study will consist of three stages:

Stage 1: from enrollment to the start of the intervention. At enrollment, eligible participants will sign informed contents and their basic information will be collected. Then they will be randomly divided into three groups (Group A, B and C). Participants in Group A and B will be taught how to use the app and sports bracelet by the researchers and required to record their diets and physical activities using the app and bracelet following their usual way of life for one week.

Stage 2: from the start of intervention (day 0) to day 44. On the morning of day 0, participants will be asked to arrive at the lab at 7:00 a.m. Measurements including anthropometry, body composition, blood pressure, fasting blood samples, dietary and physical activity data will be obtained based on standard procedures. Then, participants in Group A will receive mobile-based nutrition and exercise intervention. Participants in Group B will receive mobile-based exercise intervention. Participants in Group C will receive no interventions.

Stage 3: from day 45 to day 90. On the morning of day 45, measurements including anthropometry, body composition, blood pressure, fasting blood samples, dietary and physical activity data will be performed as day 0. Then, Group A and B will continue to receive their respective intervention and Group C will receive no intervention as before. On the morning of day 90, anthropometry, body composition, blood pressure, dietary and physical activity data will be measured and fasting blood samples will be collected for the third time. 

**Table 1 ijerph-18-04854-t001:** Summary of the trial.

Time Point	At Enrollment	After Allocation		
		Start (Day 0)	Day 45	Day 90
Enrolment				
Eligibility screen	√			
Informed consent	√			
Collection of basic information	√			
Randomization	√			
App and sports bracelet training	√			
Interventions (day 0-day 90)		√	√	√
Follow-up (day 0-day 90)		√	√	√
Assessments				
Anthropometry	√	√	√	√
Body composition (Inbody measurement)		√	√	√
Blood lipids		√	√	√
Fasting and postprandial blood sugar		√	√	√
Hemoglobin A1C		√	√	√
Blood CRP and insulin		√	√	√
Blood ALT and AST		√	√	√
Blood uric acid		√	√	√
Blood copeptin		√	√	√
Blood irisin		√	√	√
Blood adiponectin		√	√	√
Blood pressure		√	√	√
Dietary data		√	√	√
Physical activity data		√	√	√

CRP: C-reactive protein; ALT: alanine aminotransferase; AST: aspartic transaminase.

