The compliance of the subjects and the quality control will be the challenges during the study. Subjects in Group A and B will be asked to be intervened for as long as 3 months. Moreover, the elderly population whose learning ability to use mobile apps is not as good as the young may face more challenges. Poor utilization of app may cause the reduced effect of intervention [12]. In order to guarantee the compliance of them, convenient and effective methods of communication, such as telephone call, WeChat, short message and e-mail, between investigators and participants will be established. The investigators will fully explain the requirements and significance of this study to the subjects prior to the study, monitor their dietary and physical activity data and solve the problems they encounter in time. If a subject quits, the investigators will record the time and reasons timely. To ensure the quality control, participants will be trained to be familiarized with the content of questionnaires, the procedure and requirements of the trial prior to the study. If a participant fails to meet the requirements, their data will be eliminated and the reason will be recorded. Researchers will also be trained on the procedure of this trial, the content of the questionnaires and the requirements of laboratory tests. Indicators such as height, weight, waist circumference, hip circumference and blood pressure will be measured twice and the mean will be adopted as the final outcome. When filling in the FFQ, food models and photographic models will be used to enhance estimation accuracy. Blood samples will be stored at −80 degree centigrade immediately after collection to ensure the accuracy of laboratory tests. All laboratory measures will be operated by experienced staff. The conduct of this trial will be audited by a competent authority in the university every week, and the process will be independent from investigators and the sponsor. 

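### Section 2.5 does not separate stopping the intervention from ending follow-up, so programme-stoppers in Groups A and B can be lost before the day-90 BMI

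*Protocol article*

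**What the plan says.** Section 2.5 (Follow-Up) is three sentences long. The first two read: "All participants of this study will be followed-up for the duration of the intervention (three months). Participants may discontinue the trial at their request". The third is the rule at issue: "If a participant does not meet the requirements of the study, he should also discontinue the trial". Both exits are from the trial; there is no category for ending the intervention while remaining in follow-up.

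The Discussion (section 4) returns to the same people. For those who leave: "If a subject quits, the investigators will record the time and reasons timely". For those who fall short: "If a participant fails to meet the requirements, their data will be eliminated and the reason will be recorded".

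The document does not define the requirements, but most language of this kind concerns Groups A and B:

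- Section 2.4: "The exercise interventions require the subjects be provided with exercise guidance and complete around 20 min of aerobic exercise", followed by resistance exercise and a daily step target.
- Section 2.6: A and B are "required to record their diets and physical activities using the app and bracelet following their usual way of life for one week".
- Section 4, on compliance as a challenge: "Subjects in Group A and B will be asked to be intervened for as long as 3 months".

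Group C is asked only to carry on as usual (section 2.4). The primary outcome (Table 2) is the BMI difference among the three groups when the intervention ends.

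**The concern.** A day-90 comparison of randomised groups is protected by randomisation only if people are measured and analysed whatever they did with the programme. Here, someone in A or B who gives up the programme may quit the trial or be taken out of it. If so, no day-90 weight need be taken, and under the Discussion's rule a weight already taken could be discarded. Group C has no programme to stop, so this route out barely exists there. A and B would then be represented more by people who persisted, which can push the A–C and B–C differences towards the intervention.

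Two features make this worse. An undefined removal criterion may be applied by investigators who know the allocation, because section 2.3 says they cannot be blinded. And no analysis plan can recover a weight that was never measured.

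**Working it through.** **Inputs from section 2.8.** Mean BMI changes −2.8 (A), −2.5 (B), −0.9 (C) kg/m²; SD 1.4; clinically meaningful difference 1; about 200 per group, 250 after allowing for 20% dropout.

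**1. The plan's own figures.** One-way ANOVA power from the noncentral F distribution at α = 0.05 is 0.901 with 13 per group (0.873 with 12), so 13 is reproduced. Then 13 × 3 × 5 = 195, about 200, and 200/0.80 = 250. The inflation protects the number analysed; it does nothing about who is lost.

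**2. Overstatement if stoppers are lost from A and B.** Assumptions: planned changes hold for persisters; a share s stops, ends like controls (−0.9) and is not measured. Planned differences from C are 2.8 − 0.9 = 1.9 (A) and 2.5 − 0.9 = 1.6 (B). The difference in all randomised is (1 − s) × planned difference, so the overstatement is s × planned difference.

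| s | A–C, all randomised | A overstated by | B–C, all randomised | B overstated by |
|---|---|---|---|---|
| 5% | 1.805 | 0.095 | 1.52 | 0.08 |
| 10% | 1.71 | 0.19 | 1.44 | 0.16 |
| 20% | 1.52 | 0.38 | 1.28 | 0.32 |

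The 20% row treats the whole dropout allowance as stoppers.

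**3. Against the precision of the trial.** SE of a difference = 1.4 × √(2/200) = 0.14. At 10%: 0.19/0.14 = 1.4 and 0.16/0.14 = 1.1 standard errors.

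**4. Against the 1 kg/m² threshold.** At the planned effects both differences stay above 1 even at 20%. With smaller true effects, an observed difference of 1/(1 − s) corresponds to 1.0 in all randomised: 1.11 at 10%, 1.25 at 20%. With 10% stopping, an observed difference of 1.00 up to 1.11 would therefore be below 1 in all randomised.

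**5. Loss in Group C as well.** Keep 10% stoppers in A and B, and hold C at −0.9 in all randomised.

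- 10% of C lost, ending 1 kg/m² worse than the rest: observed C = −1.0; A–C 1.80 against 1.71 (0.09), B–C 1.50 against 1.44 (0.06).
- 10% lost, ending 1 kg/m² better: observed C = −0.8; A–C 2.00 against 1.71 (0.29), B–C 1.70 against 1.44 (0.26).
- 20% lost, ending 1 kg/m² worse: observed C = −1.1; A–C 1.70 against 1.71, B–C 1.40 against 1.44. The bias vanishes or slightly reverses.

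**6. If there were no true effect.** Assume 20% are removed from one group of 250 and none from the other, with the removed ending 0.5 to 1.4 kg/m² worse than those kept. The spurious difference is 0.20 × 0.5 = 0.10 to 0.20 × 1.4 = 0.28. The SE is 1.4 × √(1/200 + 1/250) = 0.133. The pairwise two-sided type I error is then about 0.12 to 0.56 instead of 0.05. This is for a pairwise comparison; section 2.9 plans a three-group test.

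**The case against.** The strongest reply is that the harmful reading is inferred. The requirements could mean eligibility or procedures common to all groups, and the elimination sentence follows one about training participants in questionnaires and trial procedures. No sentence says that missing an exercise or diet target leads to removal. Section 2.4 adapts guidance to poor compliers, with sessions "including exercise choices, duration and intensity, 3 to 5 times per week depending on the participants’ compliance", and the Discussion's stated response to poor compliance is contact and problem-solving. Section 2.5 opens by promising follow-up for all, and Table 1 lists intervention and follow-up on separate rows.

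Much of this stands. The term is ambiguous, and poor compliers who neither quit nor are removed are still due to be weighed; the concern is only with those who leave or are taken out. But the opening promise is qualified by the two sentences after it, and nothing brings leavers back for day 90. An eligibility-only reading would still remove randomised people after allocation, and one exclusion criterion in section 2.1 is unwillingness to change habits, which the programme would reveal in A and B but not in C.

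The reply also says that direction and size rest on assumptions. That is right: step 5 includes a case where losses in C cancel the bias, and stoppers may keep some benefit. This makes the bias unpredictable, not absent.

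Finally, a short article may leave detail to a fuller protocol. That would excuse silence, but here the article states a removal rule and a data-elimination rule.

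**Conclusion.** The concern holds. As written, the rules allow randomised participants to be removed for failing undefined requirements, most plausibly in A and B, without a day-90 weight in the primary comparison. Leaving on request is proper; the fault is that ending the programme and ending follow-up are treated as one event.

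The size cannot be determined from the document. The illustrative overstatement of 0.19 (A) and 0.16 (B) kg/m² depends on 10% stopping, on stoppers ending like controls, and on no selective loss in C. At the planned effects the finding of benefit would survive and the damage is to the size of the estimate; with small or absent true effects, the conclusion could change. This should be corrected, but it does not undermine the whole design. Confidence is medium because the key term is undefined.

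**What to change.** Replace the last sentence of section 2.5 with wording such as:

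> Stopping or not complying with the intervention does not end trial participation. Everyone randomised will be invited to the existing day-45 and day-90 measurements, weight at minimum, unless they withdraw consent for follow-up. These values enter the primary BMI comparison by allocated group.

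Amend the Discussion to match: where a participant falls short of the requirements, record the reason and retain the data. Both edits are needed, because otherwise the weights gained under the first could be discarded under the second. The second edit is about participants, not faulty readings: a non-fasting sample or unusable questionnaire can still be rejected.

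The cost is two text changes and a few reminder contacts through channels the Discussion already plans; no visits are added. The effect estimate will probably be smaller.

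Recovery will be partial, since some stoppers will decline to attend. Assume 80% completers, 10% unrelated dropouts who change like completers, and 10% stoppers of whom half attend day 90:

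- A: (0.80 × −2.8 + 0.05 × −0.9)/0.85 = −2.688 against −2.61 in all randomised. The remaining bias is 0.078, so about 0.11 of 0.19 is recovered.
- B: (0.80 × −2.5 + 0.05 × −0.9)/0.85 = −2.406 against −2.34. The remaining bias is 0.066, so about 0.09 of 0.16 is recovered.

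If the Discussion's elimination rule stays and is applied to these people, recovery is 0.

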### 2.6. Procedures

A summary of this trial is presented in Table 1. The study will consist of three stages:

Stage 1: from enrollment to the start of the intervention. At enrollment, eligible participants will sign informed contents and their basic information will be collected. Then they will be randomly divided into three groups (Group A, B and C). Participants in Group A and B will be taught how to use the app and sports bracelet by the researchers and required to record their diets and physical activities using the app and bracelet following their usual way of life for one week.

Stage 2: from the start of intervention (day 0) to day 44. On the morning of day 0, participants will be asked to arrive at the lab at 7:00 a.m. Measurements including anthropometry, body composition, blood pressure, fasting blood samples, dietary and physical activity data will be obtained based on standard procedures. Then, participants in Group A will receive mobile-based nutrition and exercise intervention. Participants in Group B will receive mobile-based exercise intervention. Participants in Group C will receive no interventions.

Stage 3: from day 45 to day 90. On the morning of day 45, measurements including anthropometry, body composition, blood pressure, fasting blood samples, dietary and physical activity data will be performed as day 0. Then, Group A and B will continue to receive their respective intervention and Group C will receive no intervention as before. On the morning of day 90, anthropometry, body composition, blood pressure, dietary and physical activity data will be measured and fasting blood samples will be collected for the third time. 

**Table 1 ijerph-18-04854-t001:** Summary of the trial.

Time Point	At Enrollment	After Allocation		
		Start (Day 0)	Day 45	Day 90
Enrolment				
Eligibility screen	√			
Informed consent	√			
Collection of basic information	√			
Randomization	√			
App and sports bracelet training	√			
Interventions (day 0-day 90)		√	√	√
Follow-up (day 0-day 90)		√	√	√
Assessments				
Anthropometry	√	√	√	√
Body composition (Inbody measurement)		√	√	√
Blood lipids		√	√	√
Fasting and postprandial blood sugar		√	√	√
Hemoglobin A1C		√	√	√
Blood CRP and insulin		√	√	√
Blood ALT and AST		√	√	√
Blood uric acid		√	√	√
Blood copeptin		√	√	√
Blood irisin		√	√	√
Blood adiponectin		√	√	√
Blood pressure		√	√	√
Dietary data		√	√	√
Physical activity data		√	√	√

CRP: C-reactive protein; ALT: alanine aminotransferase; AST: aspartic transaminase.

### 2.7. Outcomes

The primary outcome and secondary outcomes are presented in Table 2.

#### 2.7.1. Anthropometry

Body weight and height will be obtained at enrollment and every study visit. Body weight (kg) will be measured twice to the nearest 0.1 kg without shoes, in light indoor clothing, and standing height (cm) will be measured twice to the nearest 0.1 cm, barefoot and the head positioned in the Frankfurt horizontal plane by trained investigators using a height-weight meter (HDM-300; Huaju, Zhejiang, China) [18,19]. All participants will be asked to visit a toilet before the measurements. Overweight will be defined as 24 ≤ BMI < 28 kg/m^2^ and obesity will be defined as BMI ≥ 28 kg/m^2^ [20].

#### 2.7.2. Body Composition 

Body composition parameters include body fat mass (BFM), visceral fat area (VFA), fat free mass (FFM), body fat percent (BFP).

This outcome will be assessed with multi-frequency bioelectrical impedance analysis with 8-point tactile electrodes (InBody 720; Biospace, Seoul, Korea) [21]. Bioelectrical impedance will be measured within 2 min, standing on bare foot and grasping the hand electrodes with arms in the vertical position as is described in an article of our team [22]. Body composition will be measured at baseline, day 45 and day 90.

#### 2.7.3. Parameters of Glucose and Lipid Metabolism, C-Reactive Protein, Liver Enzymes, Uric Acid, Copeptin, Irisin and Adiponectin

These parameters will be obtained at baseline, day 45 and day 90. Serum lipids [triglyceride (TG), total cholesterol (TC), high-density lipoprotein cholesterol (HDL-C), low-density lipoprotein cholesterol (LDL-C) (mg/dL)], fasting plasma glucose (FPG), hemoglobin A1C, serum uric acid, copeptin, irisin, adiponectin, insulin and C-reactive protein will be measured after an overnight fast and 2 h postprandial plasma glucose (2 hPPG) will be measured 2 h after the breakfasts at the baseline visit, day 45 and day 90 in all participants. Plasma glucose will be measured by hexokinase method. Serum TC, HDL-C and LDL-C will be measured using an enzymatic colorimetry method. Serum TG and uric acid concentrations will be determined by colorimetric. Serum ALT and AST will be measured using International Federation of Clinical Chemistry method. Serum copeptin, irisin and adiponectin will be measured with enzyme-linked immunosorbent assay. Blood hemoglobin A1C will be measured using high performance liquid chromatography. Serum insulin will be measured using chemiluminescent immunoassay and C-reactive protein will be determined by immunoturbidimetry.

Dyslipidemia will be defined as self-reported history of dyslipidemia or levels of TC ≥ 6.2 mmol/L, LDL-C ≥ 4.1 mmol/L, TG ≥ 2.3 mmol/L, or HDL-C less than 1.0 mmol/L [23]. Impaired FPG (IFG) will be defined as 6.1 ≤ FPG < 7.0 and 2 hPPG < 7.8, and IGT will be defined as FPG < 7.0 and 7.8 ≤ 2 hPPG < 11.1. Diabetes will be defined as self-reported history of diabetes or FPG ≥ 7.0 mmol/L or 2 h plasma glucose ≥ 11.1 mmol/L on 75 g oral glucose tolerance test [24]. Elevation of serum uric acid will be defined as serum uric acid level > 420 μ-mol/L after consumption of a normal daily diet [25]. 

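### The 2-h postprandial glucose sample follows a breakfast that is not stated to be common to all groups, yet breakfast is part of Group A's intervention, so A-versus-B and A-versus-C differences can reflect the test meal

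*Protocol article*

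**What the plan says.** Section 2.7.3 sets the sampling condition for the postprandial measure in all participants: "2 h postprandial plasma glucose (2 hPPG) will be measured 2 h after the breakfasts at the baseline visit, day 45 and day 90". It does not say what the breakfast is or that it is the same for everyone.

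Section 2.4 makes breakfast part of the nutrition intervention. Subjects are given 20 g of meal replacement powder with "200 mL milk and 5 mL flaxseed oil for their breakfast and dietary guidance based on Mediterranean diet for their lunch and supper". Only one arm gets this: "Participants in Group A will receive nutrition interventions and exercise interventions for three months". Group B receives exercise alone, and Group C "will not be intervened and expected to follow their routine lifestyle as before". Table 1 marks the interventions as running at day 0, day 45 and day 90.

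Glucose parameters are secondary outcomes (Table 2). Section 2.9 compares them across the three groups by one-way ANOVA or Kruskal-Wallis test.

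Section 2.7.3 also defines glycaemic classes. IFG and IGT use the post-breakfast 2-h value. Diabetes is self-reported history, or a fasting value of at least 7.0 mmol/L, or "2 h plasma glucose ≥ 11.1 mmol/L on 75 g oral glucose tolerance test". Table 1 has a row for fasting and postprandial blood sugar but none for a glucose tolerance test, and Section 2.6 does not describe one.

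**The concern.** A glucose value taken 2 h after eating depends on what was eaten. It shows how a person handles glucose only if the load is fixed, or at least unrelated to treatment. Here the load is named as breakfast, and breakfast is one of the things randomised. If Group A takes its assigned breakfast on visit mornings while B and C eat as usual, Group A's 2-h value can differ from the others with no difference in metabolism. Group A's own change from day 0 would be affected too, if its day 0 sample followed a pre-intervention breakfast.

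What is at stake is one secondary parameter, but it bears on the first study aim in the Introduction, which includes glucose metabolism. A meal effect could be reported as a metabolic improvement. Blinded assessors and objective assays do not remove it, because the measurement is accurate and only its cause is in doubt. Nor would adjustment for food intake, listed among the covariates in the Discussion, be a reliable repair, since Group A's breakfast is set by allocation. Once the samples are taken, the problem cannot be undone.

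The second issue is one of consistency: the glycaemic definitions rely on two different 2-h tests, and only one of them is scheduled.

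**Working it through.** The plan gives no expected value, SD or sample size for 2 hPPG. Its only powered figure is for BMI and has no bearing here. The check is therefore a comparison of sections plus a carbohydrate sum.

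**Step 1. Which contrasts are exposed?**

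| Group | Assigned breakfast (Section 2.4) | Likely meal before the 2-h sample at days 45 and 90 |
|---|---|---|
| A | powder, milk, flaxseed oil | assigned breakfast |
| B | none (exercise only) | usual breakfast |
| C | none (routine lifestyle) | usual breakfast |

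The last column is the natural reading, not a stated fact. On that reading A versus B and A versus C are exposed. B versus C is not affected by an assigned breakfast. In Section 2.6 the day 0 measurements precede the intervention, so an assigned breakfast should not separate the groups at baseline.

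**Step 2. Carbohydrate in Group A's assigned breakfast.**

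- First powder, 10 g: "4.50 g protein, 0.09 g fat, 1.26 g carbohydrate and 3.00 g dietary fiber with 125 kJ in total energy".
- Second powder, 10 g: "4.65 g protein, 0.11 g fat, 1.05 g carbohydrate and 3.18 g dietary fiber with 126 kJ in total energy".
- Powders together: 1.26 + 1.05 = 2.31 g carbohydrate, and 125 + 126 = 251 kJ.
- Milk, 200 mL: the document gives no carbohydrate content. Assume 4 to 5.5 g per 100 mL, so 2 × 4 = 8 g to 2 × 5.5 = 11 g.
- Flaxseed oil, 5 mL: taken as contributing no carbohydrate (assumption).
- Total: 2.31 + 8 = 10.31 g to 2.31 + 11 = 13.31 g.
- Against a 75 g glucose load, as a scale only: 10.31/75 = 13.7% to 13.31/75 = 17.7%.

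**Step 3. Direction and size.** If usual breakfasts in B and C contain more than about 10 to 13 g carbohydrate, and Group A eats nothing further, the meal alone would be expected to lower Group A's 2-h value relative to the others. The document gives neither the carbohydrate content of usual breakfasts nor an SD for 2 hPPG, so the shift cannot be expressed in mmol/L or as a false-positive rate.

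**Step 4. Definitions against schedule (Section 2.7.3 against Table 1).**

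| Class | 2-h condition | Test it refers to | Scheduled? |
|---|---|---|---|
| IFG | below 7.8 | post-breakfast value | yes |
| IGT | 7.8 to below 11.1 | post-breakfast value | yes |
| Diabetes, 2-h limb | at least 11.1 | 75 g oral glucose tolerance test | no |

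Consider a participant with no diabetes history, a fasting value below 7.0 and a post-breakfast value of 11.1 or more. This person is above the IFG and IGT ranges and meets neither of the two usable diabetes limbs. The third limb cannot be applied because the test is not done, so the participant falls in no class. This holds whatever is eaten on visit mornings.

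**The case against.** The strongest reply is that the visit-morning meal is not stated at all. Section 2.6 has participants reach the lab at 7:00 a.m. on day 0 for measurements that include fasting blood, repeats this at day 45, and has the interventions continue afterwards. The lab might serve everyone the same meal; that is neither stated nor excluded. Section 2.4 describes the daily regimen and does not expressly say that powder, milk and oil are the whole breakfast. A journal article may also leave visit-meal detail to the full protocol. This stands in part: a reader might infer that the between-group difference must be a meal effect, and the document does not support that. It does not remove the point, because the article does more than stay silent. It names a sampling condition, and that condition coincides with a randomised component.

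A reader might also infer that the bias certainly favours Group A, or that its breakfast carries several times less carbohydrate than a usual one. Both need an assumed content for usual breakfasts; only the 2.31 g from the powders is documented.

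On the definitions, a reader might infer that diabetes cannot be classified without a glucose tolerance test. That is too strong: the three limbs are joined by *or*, and two can be applied. Nor can one say that arms will be misclassified differently in an outcome. No glycaemic class is a listed outcome, and Section 2.9 compares the parameters themselves. The stated use closest to these classes is chronic disease status as a covariate, which would precede the intervention if taken at baseline.

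**Conclusion.** The concern holds in a limited form. As written, the 2-h sample follows a breakfast that is not stated to be common, and breakfast is assigned in Group A only. The A-versus-B and A-versus-C comparisons of 2 hPPG at days 45 and 90 can therefore mix an acute meal effect with any change in glucose metabolism. This rests on one assumption: that visit-morning breakfasts follow allocation.

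Group A's assigned breakfast supplies 2.31 g carbohydrate from the powders and about 10 to 13 g in total under the stated milk assumption. The likely direction favours Group A if usual breakfasts contain more; the size is unknown.

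The scope is one secondary parameter. The primary outcome (BMI), fasting glucose, HbA1c, insulin and the B-versus-C comparison are not affected.

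The mismatch between the glycaemic definitions and Table 1 needs no assumption about the meal. It affects one limb of the diabetes definition and leaves some participants unclassifiable.

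**What to change.** Choose one of two changes for 2 hPPG:

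- **Standardise the meal.** State that all three groups eat one identical breakfast before the 2-h sample at days 0, 45 and 90. The cost is small: a common meal on three visit mornings.
- **Or remove the contrast.** Take 2 hPPG out of the between-group efficacy comparison and rest glycaemic conclusions on fasting glucose, HbA1c and insulin. The cost is one secondary parameter fewer.

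If a common visit meal is already planned, saying so in Section 2.7.3 settles this part at no cost.

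Separately, reconcile the IFG, IGT and diabetes definitions in Section 2.7.3 with the tests in Table 1. All three need attention: IFG as well as IGT uses the post-breakfast value, and the 2-h limb for diabetes refers to a test that is not scheduled. Which definition or test to use is for the investigators; the statistical requirement is that each class can be assigned from data that will be collected. If only the text changes, the cost is an edit; if a test is added to the schedule, it is that test.
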